### Process evaluation (implementation and sustainability)

Process evaluation measures include: reach (number of clients reached) and representativeness (similar demographic characteristics to the overall MOWRI client population); dose (e.g., percent completion of CHW calls; delivery and use of grocery bags; follow-through on referrals; SNAP enrollment); fidelity (e.g., quality control monitoring of a sample of CHW client calls and post-call forms; content of grocery bags); costs (e.g., CHW time; grocery bags; admin costs); participant satisfaction (e.g. usability, helpfulness, benefits, barriers). Regarding fidelity, a subset of audio-recordings of the Meals+ CHW/participant calls are automatically transcribed by the MOWRI Ring Sense, a product by RingCentral computer system. The system also translates the calls with Spanish speakers’ participants. Then the transcripts are reviewed for fidelity to the intended call content by the study team using a checklist. We are also measuring overall retention and by CHW. If issues are found, retraining and/or meetings will be held with the CHWs to improve fidelity to the call protocol. For the grocery bags, we will analyze the foods and nutrient content of the foods provided in each month’s bag based on the 2020–2025 Dietary Guidelines for Americans and MyPlate recommendations for food servings, macronutrients and micronutrients per month and per day [34, 46]. This data will be communicated to MOWRI and adjustments to the food bags will be made if necessary.

Ongoing stakeholder interviews will provide data regarding context, barriers, facilitators, usability, and burden, which will help us to measure the sustainability potential. By participating in interviews, these stakeholders provide insights about key characteristics of existing MOWRI program and clients, current program operations, internal and external communication, and organizational perspective on the integration of enhanced intervention into traditional activities, evaluating the alignment with MOWRI mission and potential concern about unanticipated effects. In addition, the Program Sustainability Assessment Tool [47] is administered to MOWRI leadership, CHW, and key stakeholders to collect quantitative results about potential sustainability of the enhanced intervention. We will analyze process data continually during the implementation phase and discuss it during project meetings to determine possible adaptations or modifications.

### Sample size and power calculations

We conducted a power analysis for this randomized controlled trial (RCT) using Statistical Analysis System (SAS) version 9.4 (Cary, NC). Assuming that the standard deviation for the primary outcome, DST, is 12.0 [48], and a significance level of $$\alpha = 0.05$$ , we will have 80.6% power to detect a difference between the arms of 2.0 points on the DST using 574 participants in each study arm. Because we are expecting 70% retention in each arm we will enroll 1640 participants in the study. We performed this sample size calculation based on assumptions from the literature.

The study uses an intent-to-treat approach so that participants who decline MOWRI program or intervention activities (i.e., deciding not to receive weekly meals from MOWRI, participate in the CHW phone calls, or receive the monthly food bags), remain in the study and will be analyzed according to their assigned intervention. Participants can stop receiving MOWRI services and still receive a follow-up call and continue to be part of the study until follow-up. Participants who are no longer getting home-delivered meals will no longer get the enhanced program of CHW calls or food bags. Participants will be withdrawn from the study if either: (1) they verbally disclose that they no longer wish to participate in the research; (2) they have not had any calls with the CHW by week 8; or (3) if they are in an institutional setting (e.g., hospitalization or inpatient rehabilitation) at the time the follow-up assessment is scheduled to occur, and this stay lasts > 14 days. In addition to the intention-to-treat analyses, we will examine the effects of the intervention among participants who would have complied with and adhered to the assigned intervention using principal stratification analysis [49, 50].

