Randomization is 1:1, with stratification of participants on living alone vs. living with others. Randomization is performed at the household level and in the case of more than one enrolled client per household, they are randomized to the same study arm. The Research Electronic Data Capture (REDCap) system randomly assigns participants within strata to one of the two conditions after the client completes the baseline survey. The assignment arm is not blinded for study team staff or participants. After randomization, the CHW tells the participant which group they were randomized to and describes the appropriate study arm processes. For participants in the Meals+ intervention group, the CHW describes the upcoming 12-week intervention and asks them to schedule a time for the first CHW coaching session within the next week. For participants in the usual care group, the CHW informs the participant that they will receive the usual MOWRI home-delivered meal service and that they will contact them in about 11 weeks to schedule a time for the 12-week call.

All plans for the design of the intervention and the evaluation were made using a CBPR approach, with decisions made jointly by University of Connecticut researchers and MOWRI leadership and staff, and additional input from community partner stakeholders. The academic-community team met at least weekly to discuss all project-related plans during the development of the intervention and to jointly solve implementation issues that arose during the pilot intervention phase.

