### Enhanced intervention components

#### CHWs

The first component of the Meals+ intervention is support from a certified CHW. The approach for CHW interactions with clients is to assess needs, identify gaps in care and resources, and then help the client through health coaching and resource coordination. Through these interactions, the CHW addresses social determinants of health, improving food and nutrition security through instrumental and social support, and increasing socialization by offering human connection. The coaching is conducted during four calls, which includes a brief form of motivational interviewing (MI), goal setting, and an action plan focused on addressing some of the client’s nutrition, health, or social issues (Fig. 1). At the final call (Week 12), CHW checks in with the client, and makes referrals to the health insurer or other appropriate community resources for any on-going or unmet needs. Then they conduct follow-up measures (diet quality, food and nutrition security, loneliness, and HRQOL) and ask about satisfaction with the intervention. Fig. 1 describes the content of each call. For any of the four coaching calls, if participants are unresponsive to multiple contact attempts from the CHW, that particular call is considered missed. The participants are contacted during the scheduled time for their next call.

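### The week-8 withdrawal rule conflicts with the intention-to-treat statement and, on its only workable reading, ends week-12 outcome collection for never-reached participants in Meals+ alone

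*Protocol article*

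**What the plan says.** All references are to the protocol article.

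- **Sample size and power calculations, intention-to-treat statement.** Participants who decline the meals, the CHW calls or the food bags "remain in the study and will be analyzed according to their assigned intervention". People who stop the meal service can still receive the follow-up call.
- **Same paragraph, withdrawal criteria.** Participants are withdrawn from the study on any of three grounds. The second is "2) they have not had any calls with the CHW by week 8". No arm is named, and the calls that count are not defined.
- **Enrollment and randomization process.** Consent, baseline assessment and notice of assignment are all handled by a CHW. Meals+ participants are then asked to book a first coaching session within a week. Usual-care participants are told that "they will contact them in about 11 weeks to schedule a time for the 12-week call".
- **CHWs (enhanced intervention components).** A coaching call that cannot be completed after several attempts counts as missed, and then: "The participants are contacted during the scheduled time for their next call". The last of the four calls is at week 12, when the outcomes are measured.
- **Planning figures.** "the standard deviation for the primary outcome, DST, is 12.0"; "we will have 80.6% power to detect a difference between the arms of 2.0 points on the DST" with 574 per arm; "Because we are expecting 70% retention in each arm we will enroll 1640 participants in the study".
- **Data analysis.** A hierarchical model uses baseline and follow-up DST, multiple imputation handles missing values, and a Bayesian principal-stratification analysis estimates the complier average causal effect. Nothing is said there about participants withdrawn under criterion (2).

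**The concern.** A Meals+ participant who avoids or never answers the coaching calls falls under both statements: one keeps that person in the study, the other withdraws them. An analysis plan cannot settle this by itself, because withdrawal decides whether the week-12 DST is collected at all.

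If the rule operates in one arm only, outcome collection in that arm depends on a post-randomisation adherence variable. Usual care contains the same kind of hard-to-reach person, and that person is still called at week 12. Meals+ outcomes would then come from a more reachable group than usual-care outcomes. The Discussion section says that barriers to adherence may fall disproportionately on those at highest nutritional risk, so the likely direction favours Meals+. The target difference is only 2.0 points, so a shift of a few tenths of a point matters.

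The complier analysis would also lose the observed outcomes of its clearest non-compliers.

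**Working it through.** **1. The plan's own figures.** SE of the difference = 12 × √(2/574) = 0.708. Two-sided power for 2.0 points = Φ(2.0/0.708 − 1.96) = 0.806, which matches the stated 80.6%. Enrolment: 574/0.70 = 820 per arm, or 1640. These figures are not in dispute.

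**2. What criterion (2) can mean.**

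| Calls that count | Who is withdrawn |
|---|---|
| Any CHW call, including consent, baseline and assignment | Almost nobody |
| Calls after assignment, both arms | Essentially all of usual care, which has no planned contact before about week 11 |
| Calls after assignment, Meals+ only | Meals+ participants never reached by week 8 |

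Only the third reading gives a working rule. It is an inference from the call schedule.

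**3. Bias under no treatment effect.** Let q be the share of otherwise assessable Meals+ participants lost through the rule, and D their mean DST deficit relative to reached participants. The documents give neither. The ranges used are assumptions: q = 5 to 10%, D = 3 to 5 points.

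- *Unadjusted complete-case contrast at follow-up:* bias = q × D.
- *Imputation from baseline DST, learned from reached Meals+ participants:* if the deficit is equally present at baseline, a fraction ρ of it is recovered, where ρ is the baseline to follow-up correlation. Bias ≈ q × D × (1 − ρ). ρ is not given; 0.4 to 0.7 is assumed.
- *SE for the second case:* 0.708 × √(1 − ρ²) = 0.649 at ρ = 0.4 and 0.506 at ρ = 0.7. This ignores the small extra variance from imputation and from the lost participants.
- *Type I error:* Φ(b/SE − 1.96) + Φ(−b/SE − 1.96), with b the bias.

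| q, D (assumed) | Complete-case bias; type I error | Imputed bias, ρ = 0.7 to 0.4; type I error |
|---|---|---|
| 5%, 3 | 0.15; 5.5% | 0.045 to 0.09; 5.1 to 5.2% |
| 5%, 5 | 0.25; 6.4% | 0.075 to 0.15; 5.3 to 5.6% |
| 10%, 3 | 0.30; 7.1% | 0.09 to 0.18; 5.4 to 5.9% |
| 10%, 5 | 0.50; 10.9% | 0.15 to 0.30; 6.0 to 7.5% |

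**4. Bias when there is a real effect.** Suppose reached participants gain 2.0 points and unreached participants gain nothing. At q = 10% the as-randomised difference is 0.90 × 2.0 = 1.80. Imputing the unreached from reached Meals+ participants credits them with the effect, which adds q × 2.0 = 0.20 points to the bias in step 3. At D = 5 the total is 0.20 + 0.15 to 0.20 + 0.30, that is 0.35 to 0.50 points.

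**The case against.** The strongest case on the other side has five parts.

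- **The conflict is narrow.** Someone who tells the CHW that they do not want coaching has had a call, so criterion (2) does not touch them. This stands. A reader might infer that the rule strips all non-compliers from Meals+; it does not. Those who decline by phone and those who take only some calls stay in. The overlap is confined to people who never speak to the CHW after assignment.
- **No arm is named.** This also stands: application to Meals+ alone is inferred. But the alternatives withdraw either almost nobody or a whole arm, so the ambiguity is itself a defect.
- **Withdrawal is not exclusion from analysis.** A reader might infer that withdrawn participants leave the analysis set. The article does not say so. Everyone randomised has a baseline DST, imputation is planned, and further detail may lie in an analysis plan that is not shown. What remains is that their week-12 DST would not be sought.
- **The planned analysis uses baseline.** A stable deficit is partly recovered by baseline-informed imputation, and a change-score contrast among completers would be essentially unbiased by it. So 10.9% describes an unadjusted complete-case contrast and should not be carried over to the planned analysis. The protection depends on the deficit being stable. Crediting non-recipients with benefit inflates a real effect but does not create a false positive under the null.
- **The complier analysis survives.** Never-contacted people remain identifiable from call records, some decliners' outcomes are still observed, and sensitivity to the identifying assumptions is planned. A reader might infer that the analysis becomes impossible; it only leans more on assumptions.

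The equal 70% retention figure is a planning assumption that may already include these losses, so the documents do not show it to be wrong.

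**Conclusion.** The two statements are incompatible for Meals+ participants who are never reached after assignment, and they must be reconciled. On the only workable reading, the rule stops week-12 outcome collection in one arm on an adherence variable. This can bias the primary comparison, probably in favour of Meals+; the sign would reverse if unreached people eat better than reached ones.

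The size cannot be fixed from the documents. Under no effect and the assumed ranges, an unadjusted complete-case contrast is biased by 0.15 to 0.5 points. With baseline-informed imputation, the least favourable pair considered (10%, 5 points) leaves 0.15 to 0.30 points, or 7.5 to 15% of the 2.0-point target, and type I error of about 6.0 to 7.5%. At smaller q or D the inflation is slight. Imputation reduces the problem without fully repairing it.

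This should be fixed. It does not by itself invalidate the trial, but outcomes that are never collected cannot be recovered by later analysis.

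**What to change.** - Delete criterion (2) as a ground for withdrawal from the study. Record no CHW contact by week 8 as a non-adherence flag in Meals+, and define which calls count.
- Attempt the week-12 assessment in every randomised participant who has not withdrawn consent, and analyse all participants in their assigned arm. This point makes no case for changing criterion (3).
- Use the flag in the principal-stratification analysis and in the imputation model, so that unreached participants are not imputed as if they had received the intervention.

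This concerns outcome collection and analysis only. Whether coaching or bags continue after week 8 is for the sponsor to settle.

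The cost is a minor IRB amendment, for which the protocol already provides a route, and extra call attempts to what may be a small group, some of whom will not be reached. The estimated effect may be slightly smaller, because people who received no coaching would count in Meals+, as intention-to-treat requires.

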## Background

Food insecurity is defined as a lack of access to enough food to maintain an active and healthy life [1]. In 2023, 13.5% of households in the United States were food insecure [1]. This number was higher for low-income older adults living alone, with 29% of those living below the poverty line experiencing food insecurity [1]. Among older adults, food insecurity is associated with poorer diet quality and higher rates of chronic disease [2, 3]. Some older adults experiencing food insecurity must choose between spending money on food or medication, which further compromises their health [4].

It is common for older adults to suffer from numerous nutritional deficiencies and have difficulty reaching their daily nutrient intake goals [5]. A longitudinal study among older adults observed that those with food insecurity had significantly lower Healthy Eating Index (HEI) scores, which implies lower diet quality and higher prevalence of nutritional deficiencies [6, 7]. In this sense, many older adults have difficulties in managing their own nutritional needs and could benefit from food programs, such as home-delivered meal programs [4, 8].

Home-delivered meal programs (HDMP) are among the tools used to combat food insecurity among older adults and other at-risk groups [9–12]. Community-based HDMP delivers healthy meals to older adults to improve diet quality and promote independent living, while also providing informal daily well-being checks. This can result in reduced hospitalizations, shorter hospital stays, fewer readmissions, and ultimately, lower healthcare costs [11, 13]. Systematic reviews of observational and intervention studies demonstrate that HDMP may also impact older adults’ quality of life, by reducing frailty, loneliness, and risk factors that exacerbate chronic diseases [10, 14]. The psychosocial benefits of HDMP derive from the interface between the community-based workforce and older adults in their homes, connecting them with food and health services [15–18]. Many older adults have few social ties, which makes the work of HDMP paid and volunteer drivers essential for social interaction through daily informal well-being checks [18, 19].

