#### Secondary outcomes

Secondary outcomes include food security, nutrition security, loneliness, and HRQOL. Food security is measured by the United States Department of Agriculture (USDA) 6-item Household Food Security Scale [41]. The scores represent the number of affirmative responses (0–6) with individuals classified in 3 different categories: 0–1 indicates food security, 2–4 indicates low food security, and 5–6 indicates very low food security.

Nutrition security is measured by a 2-item Nutrition Security Screener (NSS) developed by Tufts University, Kaiser Permanente, and Los Angeles Department of Public Health [42]. The NSS includes a short preamble to help with the definition of healthy foods for the respondent, listing examples of foods that support health and well-being. The first question is: “Thinking about the last 3 months, how hard was it for you or your household to regularly get and eat healthy foods?”. The “somewhat hard” respondents are classified as “low nutrition security”, and the “hard” or “very hard” responses are classified as “very low nutrition security.” The “not very hard” or “not hard at all” are classified as “high nutrition security.” The second part of the survey is composed of 13 questions related to the barriers faced by individuals to access healthy foods and are analyzed through binary responses (e.g. “The price of healthy foods limits your ability to eat healthier meals” and “Not having information about which foods are healthy limits your ability to eat healthier meals”).

Subjective isolation or loneliness is measured by the validated University of California, Los Angeles (UCLA) 3-Item Loneliness Scale [43]. The three questions are related to the three dimensions of loneliness (relational connectedness, social connectedness, and self-perceived isolation), with the following content: “How often do you feel that you lack companionship?”; “How often do you feel left out?”; and “How often do you feel isolated from others?”. The score classifies individuals into two different groups: “not lonely” (scores 3 to 5) and “lonely” (scores 6 to 9). The scores of each question are added to generate an individual score.

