Health-related quality of life is measured by the Centers for Disease Control and Prevention 4-question measure. The questions explore self-reported general health status (e.g. “Would you say that in general your health is…”) and calculate the number of unhealthy days during the month. The estimation is calculated based on the number of unhealthy physical and mental days. Considering the unhealthy days measure, the participants will be classified into two different groups: “less than 14 days” or “greater than or equal to 14 days” [44].

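### Withdrawing participants who are in a long institutional stay at follow-up loses data in a health-dependent way, probably concentrated in the worse HRQOL class and possibly uneven between arms

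*Protocol article*

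**What the plan says.** Under Sample size and power calculations, the protocol article lists three grounds for removal, introduced by "Participants will be withdrawn from the study if either". The third applies to participants "if they are in an institutional setting (e.g., hospitalization or inpatient rehabilitation) at the time the follow-up assessment is scheduled to occur", provided that the stay exceeds 14 days. This is withdrawal from the study, not only from services. The same paragraph commits to intent-to-treat: people who decline meals, calls or bags stay in the analysis as assigned, and people who stop the meal service can still have the follow-up call.

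Under Secondary outcomes, the HRQOL questions cover general health and also "calculate the number of unhealthy days during the month", counting physical and mental days. On that count "the participants will be classified into two different groups", with the worse one "greater than or equal to 14 days". HRQOL is one of four listed secondary outcomes: "Secondary outcomes include food security, nutrition security, loneliness, and HRQOL".

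On hospital use, the Background says of home-delivered meals: "This can result in reduced hospitalizations, shorter hospital stays, fewer readmissions". Further on, it credits CHWs with a favourable effect on outcomes that include hospitalisations. Under Usual care condition, that arm receives its single CHW support call only after the follow-up assessment.

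Under Data analysis, missing values are to be multiply imputed. The article does not say whether people withdrawn for a long stay remain in the analysis set.

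**The concern.** The rule acts after randomisation and on a health state. Someone institutionalised for more than two weeks around the follow-up date is likely to report many unhealthy days, so the missing answers should fall mainly in the worse HRQOL class. Each arm's HRQOL would then look better than it is.

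The arm comparison is also exposed. Until follow-up, CHW coaching is part of what separates the arms, and the article itself links CHWs to hospital use. If Meals+ shortens or prevents long stays, the rule hides part of the benefit. If it lengthens stays or makes them more frequent, the rule favours Meals+.

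The rule sits badly with the intent-to-treat commitment beside it: people who refuse the intervention are followed, but people who fall ill for long enough are not. An analysis plan written later cannot recover answers that the protocol tells staff not to collect.

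**Working it through.** **The plan's own figure.** With SD 12.0, a difference of 2.0 and 574 per arm, the standard error is 12 × √(2/574) = 0.708. Then 2.0/0.708 − 1.96 = 0.863, which gives 80.6% power (two-sided 0.05). Enrolment is 574/0.70 = 820 per arm, or 1640. Both figures reproduce. The point does not depend on them, and the fix does not change them.

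**Inputs for the HRQOL class.** The article gives none of these, so all are assumptions:
- q, the share of an arm withdrawn for a long stay: 2–10% (about 16 to 82 of 820)
- r, the probability of 14 or more unhealthy days among those withdrawn: 0.80–1.00
- p, the same probability among everyone else: 0.30–0.50

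Other attrition is ignored, and p is taken as equal in both arms, so no other treatment effect is present.

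**Formulas.**
- Class rate with everyone counted: q·r + (1 − q)·p
- Rate if the withdrawn are left out, or imputed exactly like people at home: p
- Understatement in an arm: q·(r − p)
- Between-arm difference hidden: (q in usual care − q in Meals+)·(r − p)

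**Understatement per arm.** Smallest: 0.02 × (0.80 − 0.50) = 0.6 points. Largest: 0.10 × (1.00 − 0.30) = 7.0 points.

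**Difference hidden.**

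| p | r | q usual care | q Meals+ | Full rate, usual care | Full rate, Meals+ | Hidden difference |
|---|---|---|---|---|---|---|
| 0.50 | 0.80 | 3% | 2% | 50.9% | 50.6% | 0.3 points |
| 0.40 | 0.95 | 5% | 3% | 42.75% | 41.65% | 1.1 points |
| 0.30 | 1.00 | 10% | 6% | 37.0% | 34.2% | 2.8 points |
| 0.40 | 0.95 | 5% | 5% | 42.75% | 42.75% | 0 |

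The last row marks the limit of the argument: with equal q and no differing effect among those withdrawn, each arm is understated but the comparison is not biased.

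**Effect of imputation.** Suppose the imputation model predicts a rate p* for the withdrawn, somewhere between p and r. The understatement becomes q·(r − p*). Baseline predictors may move p* part of the way towards r. Under missing at random, without institutional status in the model, there is little reason for p* to reach r.

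**Scale.** With 574 per arm, the difference in class rate detectable at 80% power is about 7.5 points at p = 0.30, 8.0 at 0.40 and 8.3 at 0.50.

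**The case against.** Several stronger readings are tempting, and the document does not support them.

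- **That those withdrawn are almost certain to be in the worse class.** The rule does not require the 14 days to have passed before the scheduled date. A person admitted two days before the call who stays 15 days is withdrawn, yet only two institutional days lie in the recall month at that date. The measure is self-reported and the setting includes rehabilitation. Likely is defensible; certain is not.
- **That the sentence on meals and hospital use shows the arms will differ.** Both arms receive the meals. Only the statement about CHWs bears on a difference, and it makes one plausible without showing it.
- **That these people leave the analysis, so intent-to-treat is broken.** Multiple imputation is planned, and nothing says that withdrawal removes anyone from the analysis set. The intent-to-treat sentence is about people who decline services. The tension is real, but a contradiction is not established.
- **That a true effect is erased.** This needs unequal long-stay rates, no other effect, and imputation that treats the withdrawn like people at home.

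It is also fair to say that the 14-day class is not named as the only HRQOL analysis, that some institutionalised people would be unreachable anyway, and that the detail of an imputation model commonly belongs in the analysis plan. These objections limit the size of the point. They do not remove it, because the rule itself stops collection of answers that could be obtained.

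**Conclusion.** The point holds in a limited form. The rule causes a health-dependent loss of follow-up after randomisation, likely concentrated in the class with 14 or more unhealthy days and possibly different between arms. Under the assumed ranges, each arm's class rate is understated by about 0.6 to 7 points. A between-arm difference of about 0.3 to 2.8 points is hidden if Meals+ lowers long stays by 1 to 4 points, and none if long stays and effects among these people are the same in both arms.

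These sizes rest wholly on assumed rates, and they are upper values to the extent that imputation recovers part of the gap. They are small beside the roughly 7.5 to 8.3 points the trial could detect, and the argument concerns a secondary outcome. The same rule also discards follow-up DST answers, but no bias in the primary outcome is shown here. The change is still worth making because it is cheap and removes an avoidable source of informative missingness.

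**What to change.** Replace the third withdrawal ground with a category for follow-up missed or delayed because of an institutional stay. Then:

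- State that these participants remain in the intent-to-treat set.
- Attempt the follow-up call within a stated extended window.
- Record long stays and report their number by arm. Applying the present rule already requires staff to learn the length of stay.
- Use institutional status in the imputation model.
- Add one HRQOL sensitivity analysis that either places those without an answer in the 14-or-more-days class or imputes them under a not-at-random assumption.

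DST may stay missing where diet at home cannot be reported. Assigning the worse class need not become the main HRQOL analysis: it would make the endpoint partly composite, a trade-off the team may reasonably decline.

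The cost is a change of wording, a few later calls, some assessments off the 12-week schedule and one extra analysis. Sample size and DST power do not change.
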